Specific Aim 3: Analyze biomarkers of efficacy and explore whether TRE has beneficial effects on behavioral, cognitive, and motor function outcomes using standard HD clinical scales.

Hypothesis 3: We hypothesize that TRE will show trends toward improvements in biomarkers of HD progression and clinical measurements of these outcomes.

The aims will be accomplished by use of a 12-week prospective interventional open-label, single-arm trial that includes both field and in-laboratory data collection in persons with premanifest and early manifest HD. Specifically, participants will be asked to engage in a TRE diet, maintaining a 6-8-hour eating window every day for 13 weeks (+/- 1 week). A baseline (within 1-3 weeks of trial onset) and follow-up (within 7 days after week 12 of TRE) visit will assess body composition, safety labs, vital signs, clinical features of HD, and blood biomarkers. Participants will track the timing and content of diets, and record at-home body weight, physical activity, sleep, and mood using established survey techniques [11, 12].

*Primary endpoints: Feasibility, Safety, and Preliminary Efficacy*

Feasibility and tolerability: We expect that > 80% of subjects will adhere to the diet for the duration of the study with limited to no adverse events.

Body weight and fat-free mass: We expect that subjects will maintain their body weight and fat-free mass over the course of the 12-week study. Specifically, we hypothesize that at least 90% of subjects will have no more than a 10% loss in total body weight and no more than 5% loss in fat-free mass.

Vitals and blood chemistries: We expect that subjects will not experience adverse changes in vital signs, or measures of liver, kidney, or metabolic function.

Plasma neurofilament light protein (NfL) and Glial fibrillary acidic protein (GFAP): We expect that there will be an improvement in measures of plasma NfL and GFAP from baseline to follow-up.

*Secondary endpoints: Clinical Efficacy and Mechanism of Action*

Unified Huntington’s Disease Rating Scale (UHDRS) clinical assessment: We expect to see minor improvements in UHDRS motor, cognitive, independence, and functional capacity assessments; however, given the short-term nature of the study, it is unlikely significant changes will be observed.

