The primary aim of this study is to assess the feasibility, safety, and preliminary biomarker efficacy of a TRE diet in persons with HD. We will also explore clinical efficacy and potential mechanism of action. The proposed study will be a prospective interventional, open-label, single-arm trial (Fig 1). After baseline testing and a 1-3 week lead-in period, enrolled participants will be asked to engage in a TRE diet, specifically maintaining a 6-8-hour eating window every day for 13 weeks (+/- 1 week). Participants will be allowed to self-select the timing of the eating window, but once selected, they will be asked to maintain that schedule at minimum 5 of 7 days for the duration of the study. Outside of that window, for the remaining 16-18 hours of day/night, participants will be asked not to consume calorie-containing food or drink. Beverages without calories will be allowed. We will measure body weight and composition, safety labs, adherence to the diet, dietary composition, sleep, physical activity, mood, and markers of efficacy. If our primary measure of safety, as represented by stable body weight and fat-free mass, is not maintained, the study will be halted immediately. Data collection episodes will take place at the OHSU Department of Neurology outpatient clinic area within 1-3 weeks prior to the start of the study, and again within 7 days after 12 weeks of TRE. Participants will complete study surveys directly in Qualtrics. Survey invitations and reminders will be sent by email or SMS text message to study participants. A maximum of 3 reminders will be sent to a participant for any incomplete form. Participants will be contacted via phone call if there are 2 or more days without completing meal tracking surveys.

1. Safety, Biomarkers, and Clinical Efficacy: At baseline (within 1-3 weeks of trial onset) and follow-up (within 7 days after week 12 of TRE) participants will visit the OHSU Department of Neurology clinic for body weight assessment and body composition analysis via bioelectrical impedance analysis. Vitals will be measured by a trained researcher and blood will be drawn to obtain safety labs (chemistry and hematology panel, lipids, A1c, blood glucose, and creatinine clearance) and blood samples for biomarker assessments of efficacy. Participants will then be assessed by a trained medical professional using the Unified Huntington’s Disease Rating Scale (UHDRS).

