2. Diet Adherence and Sleep: A daily electronic survey will be sent to each participant via text message or email, depending on participant preference, in the evening at 19:00 h. Participants will be asked to report the time of day they started and stopped eating, and their sleep habits and sleep quality from the previous night.
3. Dietary Composition: Twice per week, participants will be asked to use the SnapCalorie^TM^ phone application to record the meals eaten in a given day. At the baseline visit, participants will be instructed how to download and use the phone application. A text or email reminder will be sent in the morning at 07:00 h on the days that the participants are asked to record their meals.
4. Weekly Survey: Participants will be asked to complete weekly surveys to measure self-reported body weight, mood, and physical activity. The survey will be completed via Qualtrics. Researchers will send reminder text messages each week with a link to the relevant survey.
5. Safety and Tolerability: At the baseline visit, participants will be given a scale to measure at-home body weight. Every other week during the 12-week study, participants will be contacted by telephone to assess at-home body weight and discuss adherence issues or any adverse events. If a participant loses more than 10% of their total body weight, they will be asked to stop the TRE diet and return to their prior dietary habits.

[figure not shown]

**Figure 1**. TRE in HD Study Design

5. Study Population

1. Number of Subjects

We will recruit 40 participants expecting roughly 25 participants to meet inclusion criteria with the goal of yielding a final sample of at least 20 in the experimental condition after a conservative expected level of attrition (~20%). These individuals will consist of males and females 21 years of age or older, with genetically confirmed premanifest or early manifest (stage I and II) HD defined by a CAP score greater than 368 or UHDRS TFC greater than or equal to 7, respectively. Subjects will be recruited from Oregon and Washington. See Statistical Analysis Section for justification of the selected sample size.

1. Inclusion and Exclusion Criteria

Inclusion Criteria

Subjects eligible to participate in this study are persons who:

1. Are of at least 21 years of age at Screening.

2. Must fulfill one of the following criteria:

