1. **Lead-in Period:** During the 1-3 week lead-in period after the baseline visit, participants will be asked to use the SnapCalorie^TM^ phone application and to complete the daily meal timing and sleep survey to log at least 7 days of their normal dietary and sleep habits. Daily calories and macronutrients will be calculated and used to provide dietary caloric goals during the 12-week TRE intervention.
2. **Time-Restricted Eating Protocol:** During the baseline visit, participants will meet with researchers and be informed of the intervention. They will be instructed to maintain a 6-8-hour eating window every day for 12 weeks after completion of the lead-in period. Participants will be allowed to self-select the timing of the eating window, but once selected, should attempt to maintain the schedule at a minimum 5 of 7 days per week for the duration of the study. Outside of that window, for the remaining 16-18 hours of day/night, participants will be asked not to consume calorie-containing food or drink. Beverages without calories, such as black coffee or tea, will be allowed. Participants will be instructed to consume plenty of water and electrolytes. Participants will also be provided a document with information about general healthy diet and exercise habits, in addition to instructions about the TRE protocol and a brief overview of each study visit..
3. **Daily Participant Tasks:**

*Meal Timing and Sleep Survey:* A daily electronic survey will be sent to each participant via text message or email, depending on participant preference, in the evening at 19:00 h. Participants will be asked to report the time of day they started and stopped eating, and their sleep habits and sleep quality from the previous night. Specifically, they will be asked to report their sleep duration, quality, and number/length of naps that day.

1. **Weekly Participant Tasks**:

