     3. **Specimen Handling:** Blood samples will be identified only by the code assigned at the initial phone screen. Processing and handling of blood samples will be done by the OCTRI nursing and core lab staff. Samples will be stored and maintained by the [name] Lab -80 degree freezer. Access to study samples at OHSU will be limited to OCTRI core lab staff and study personnel listed on the IRB approved protocol. Coded biological samples may be sent to the Quanterix Corporation Laboratory for analysis.
   1. Sharing of Results with Subjects

With their consent, we will make known to the participant some of the information we have gathered from the physiological testing during the study. There is a chance that the study assessments and/or lab results will reveal some medical abnormality. This information will be conveyed to the participant, together with a recommendation to discuss the results with a physician if appropriate. All blood data collected and shared with participants is from a CLIA certified lab (OHSU).

- 1. Data and Specimen Banking

Venous blood samples will be stored for future research, which may include genetic research.

Samples will be hand carried by the study staff to the Hatfield Research Center and stored in secure freezers room for storage. Any remaining specimens after the required analyses have been conducted will be stored securely in the Hatfield Research Center. Samples may be shared with other investigators at OHSU or investigators outside of OHSU. All appropriate and required agreements will be in place prior to the release of samples. Samples will be identified by an assigned study participant ID number and will be transported by an approved courier. For any future use of these samples, IRB approval must be obtained. The repository guardian will be [name], who will be responsible for managing future access to these samples.

8. Data Analysis

The primary goals of this study are to assess if TRE in persons with premanifest and early manifest HD is 1) feasible, 2) safe, and 3) potentially efficacious.

Specific Aim 1: Examine the feasibility and tolerability of TRE for treating HD.

The percent of adherent days to the TRE intervention will be calculated and any adverse events will be recorded and described in detail.

Specific Aim 2: Evaluate the safety of TRE in premanifest and early manifest HD by measures of nutritional status.

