The primary safety outcome will be percent change in body weight and fat-free mass which will be examined using planned comparison paired t-tests between the baseline and follow-up visits. Differences in measures of vital signs, and safety labs will also be examined using planned comparison paired t-tests between the baseline and follow-up visits as additional safety measures.

Specific Aim 3: Explore whether TRE has beneficial effects on biomarkers of disease progression and behavioral, cognitive, and motor function outcomes using standard HD scales.

Differences in measures of blood biomarkers and UHDRS clinical scores will be examined using planned comparison paired t-tests between the baseline and follow-up visits.

Table 3. Statistical Analysis

| Measure | Statistical Test (for each measure) |
| --- | --- |
| Daily eating period (length of time) | Paired t-test from Baseline to Follow-up |
| Adherent days | Percent of days adherent to the TRE diet |
| Adverse events | Descriptive statistics |
| Body weight | Paired t-test from Baseline to Follow-up |
| Fat-free mass | Paired t-test from Baseline to Follow-up |
| Vital signs (Temp, BP, HR, RR, O2) | Paired t-test from Baseline to Follow-up |
| Safety labs (LFTs, Cr and BUN, CMP, A1c, BG, Lipids) | Paired t-test from Baseline to Follow-up |
| Biomarkers (NfL and GFAP) | Paired t-test from Baseline to Follow-up |
| UHDRS | Paired t-test from Baseline to Follow-up |
| Dietary composition | Descriptive statistics |
| Self-reported sleep habits | Descriptive statistics |
| Self-reported physical activity | Descriptive statistics |
| Mood | Descriptive statistics |

1. Sample Size, Expected Outcomes, and Translation of Results

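### The 19:00 survey that measures adherence can miss evening eating, because the protocol does not say which day the eating times cover or that the form be answered after the last intake

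*Protocol*

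**What the plan says.** Protocol Section 4 (Study Design, item 2) and Section 6 (Daily Participant Tasks) both describe a daily electronic survey sent "in the evening at 19:00 h. Participants will be asked to report the time of day they started and stopped eating". The same form asks about sleep on the previous night. Section 6 adds that "they will be asked to report their sleep duration, quality, and number/length of naps that day". Neither section attaches a day to the eating times.

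On the window itself, Section 4 states "Participants will be allowed to self-select the timing of the eating window". The window is 6-8 hours long, and "for the remaining 16-18 hours of day/night, participants will be asked not to consume calorie-containing food or drink". No latest start or closing time is given.

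The survey data feed two outcomes:

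- Adherence. Section 2 lists it among the primary endpoints: "We expect that > 80% of subjects will adhere to the diet for the duration of the study". Section 8 gives the analysis: "The percent of adherent days to the TRE intervention will be calculated".
- Length of the daily eating period. Table 3 assigns it a paired t-test from baseline to follow-up.

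Section 6 uses the same survey in the lead-in to log at least 7 days of usual habits. Section 4 allows up to 3 reminders for an incomplete form and a telephone call after 2 or more days without meal tracking. It states no time at which a form closes.

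**The concern.** The time at which eating stopped can be reported correctly only once eating has stopped. A survey that arrives at 19:00, combined with a window the participant may place anywhere, will reach some participants while the window is still open. It will reach others after the window has closed but before any late snack. Eating outside the window is what makes a day non-adherent, and a form already answered at 19:00 cannot show that it happened later that evening.

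At stake is the accuracy of a primary feasibility measure and of the one tested measure of how far the diet shortened the eating day. The send time and the free choice of window are both fixed in the protocol, so this is a stated design choice and not a detail left for later.

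**Working it through.** **Inputs.** Send time 19:00 (Sections 4 and 6); window length 6-8 h and fasting period 16-18 h (Section 4); window placement free (Sections 4 and 6).

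**1. The plan's own figure.** 24 - 8 = 16 h and 24 - 6 = 18 h. The stated fasting period agrees with the window length.

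**2. Which windows are open at 19:00.** A window is still open if start + length > 19:00, that is, if start > 19:00 - length.

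- 8 h: start after 11:00
- 7 h: start after 12:00
- 6 h: start after 13:00

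**3. What is recorded if the form is answered at 19:00 with the last intake so far.** Where eating is continuous across 19:00, recorded length = min(stop, 19:00) - start. Where there is a gap, the recorded stop is the last intake before 19:00. Adherent is taken here as 8 h or less.

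| Day actually eaten | True length | Recorded length | Classified |
|---|---|---|---|
| 12:00-22:00 | 10 h | 7 h | wrongly adherent |
| 11:00-21:00 | 10 h | 8 h | wrongly adherent |
| 09:00-17:00, snack at 21:00 | 12 h | 8 h | wrongly adherent |
| 10:00-20:00 | 10 h | 9 h | correctly non-adherent |
| 12:00-20:00 | 8 h | 7 h | correctly adherent |

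The third row shows that early windows are exposed too. The last two show that a shortened record does not always change the classification.

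**4. How many windows are exposed.** The documents give no distribution of chosen windows. If start times were uniform between a and b (an assumption), the share of 8 h windows open at 19:00 would be (b - 11)/(b - a), with a floor of 0:

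- 06:00-11:00: 0/5 = 0%
- 07:00-12:00: 1/5 = 20%
- 08:00-13:00: 2/5 = 40%
- 09:00-14:00: 3/5 = 60%

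**5. Possible effect on percent of adherent days.** Let p be the true share of adherent days and q the share of non-adherent days misread as adherent. Recorded share = p + (1 - p)q. With p = 70% (assumed):

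- q = 0: 70%
- q = 0.25: 70 + 30 × 0.25 = 77.5%
- q = 0.5: 70 + 30 × 0.5 = 85%
- q = 1: 100%

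The effect runs from none to large, and nothing in the documents locates q.

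**6. The paired comparison of eating period.** If the lead-in record is short by b hours and the on-diet record by t hours, recorded reduction = true reduction - (b - t).

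- Lead-in 08:00-21:00 (13 h, recorded 11 h, b = 2); on diet 11:00-19:00 (8 h, t = 0). True reduction 5 h, recorded 3 h.
- Lead-in 08:00-19:00 (11 h, b = 0); on diet 12:00-20:00 (8 h, recorded 7 h, t = 1). True reduction 3 h, recorded 4 h.

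The sign of the error depends on whether b or t is larger.

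**The case against.** The strongest reply is that 19:00 is when the survey is sent, not when it is answered. Reminders are foreseen and no deadline is given, so a participant may well complete the form after the last meal. The eating times might also be meant for the previous day, or participants might enter a planned stop time. This stands to the extent that shortening of the record is a possibility, not an established fact. It does not remove the gap. Reminders go only to those who have not answered, so the prompt participant stays exposed. The text ties the previous night to sleep only, which makes same-day eating the plain reading. If the previous day was meant, the protocol does not say so.

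A second reply is that other sources would reveal late eating: the twice-weekly meal photographs, the telephone call every other week about adherence, and the paper meal timing diaries mentioned in Section 7. These mean that late eating need not go wholly unrecorded. None of them is stated to correct the daily stop time.

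A reader might also infer several stronger conclusions that the documents do not support:

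- *That many windows are cut off.* No distribution of windows is given, and the assumed ranges above run from 0% to 60%.
- *That the error can only inflate adherence.* If a day under 6 h counts as outside the 6-8 h window, a 14:00-22:00 day (8 h) recorded as at most 5 h would be wrongly called non-adherent.
- *That the error can be measured against the 80% target.* That target is a share of participants, the recorded quantity is a share of days, and the protocol gives no rule linking the two.

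**Conclusion.** The point holds as a measurement weakness. Followed as written, the survey can miss evening eating for any participant who answers promptly, with early or late windows alike, and nothing in the protocol prevents or repairs this. Overstatement of adherent days is the probable direction, because the eating missed is eating that would lengthen the recorded day. That direction assumes prompt answers for the same day, reporting of the last intake so far, and short days not being counted as breaches.

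The size cannot be estimated from the documents. The percentages in the working show how wide the range is and are not predictions. For the baseline-to-follow-up test of eating period, even the direction is uncertain, because both periods can be shortened. This test is taken to use the lead-in as its baseline, since Table 1 places the survey in the lead-in and daily columns only.

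This is a cheap improvement to a primary feasibility measure. It is not a demonstration that the adherence result will be wrong.

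**What to change.** Send the survey the next morning and ask for the first and last calorie intake of the whole previous day, with the previous night's sleep and the previous day's naps. Alternatively, keep the evening send, state that the eating times refer to that day, and require the form to be completed, or the entry corrected, after the last intake. In either case, use the same timing and wording in the lead-in as on the diet.

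The cost is a changed send time and revised question wording, with no added visit or procedure. The downside of the morning version is slight next-day recall error, which deserves some weight in a population that may have cognitive impairment. The evening version with a correction step avoids most of that, but relies on participants returning to the form.

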10. Are not weight stable for at least three months prior to enrolling in the study, defined as greater than 2 kg change in body mass.

11. Express a desire to lose weight during the study.

12. Have a clinically significant medical, surgical, laboratory, or behavioral abnormality which in the judgment of the site Investigator makes the subject unsuitable for the study.

13. Have consistently practiced a time-restricted eating protocol within 3 months of trial onset.

In the event of a screen failure, data acquired will be destroyed immediately.

1. Vulnerable Populations

Persons with HD are a potentially vulnerable population; however, the focus on premanifest and stage I/II disease and cognitive requirements for study inclusion should limit the probability of working with those that are particularly vulnerable.

1. Setting

All research will be performed at OHSU and the research facilities at OCTRI.

1. Recruitment Methods

Subjects will be recruited through the OHSU Movement Disorders clinic patient pool using a combination of approaches, including clinician recruitment and referral during clinic appointments, matching from an IRB approved research registry (OHSU IRB #8049), advertising via an IRB approved flyer, and contacting participants of Enroll-HD (OHSU IRB #21855). Potential participants will be contacted either directly in clinic or by phone, utilizing an IRB-approved phone script.

Based on both recruitment methods and knowledge of the OHSU Movements Disorders HD patient population demographics, we do not anticipate identifying or enrolling any non-English speaking participants. However, if a participant is identified, study staff will obtain translation of the consent form, and will utilize translation services to conduct the study surveys verbally. We would not be able to obtain data via the SnapCalorie^TM^ app, as it is not available in languages other than English.

Participants will be paid for their participation in the study, up to $75 total if they complete the entire study -- $25 for completion of the Baseline visit, $25 for completion of the Follow-up Visit, and $25 as a Study Completion Bonus. If participants do not complete the study, they will be paid for the visits they do complete.

1. Consent Process

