Potential participants will first be contacted by phone and study staff will utilize an IRB-approved phone script to assess initial interest and eligibility for the study. Those who remain interested and eligible will be provided the consent form for review. The potential participant will be contacted by phone a few days later and if still interested, will be scheduled for a baseline visit in clinic. At the baseline visit, investigators will go over each aspect of the consent form in plain English and answer any questions the participants may have. When the participant is satisfied with his/her understanding of the study, and fully comprehends his/her freedom to withdraw at any time, the potential participant will be asked to sign the paper research consent form if they wish to do so.

The investigators will take all necessary steps to answer questions raised by volunteers pertaining to the nature, purpose and risks of the study. An investigator will be available at all times to answer questions the participant may have. By both verbal and written instruction, the participant will be explicitly informed of his/her freedom to withdraw consent and discontinue participation in the project at any time.

6. Procedures Involved

1. **Baseline and Follow-up Visits:** 1-3 weeks prior to the onset of the study and after week 12 of TRE, participants will visit OHSU where the following procedures will take place:

*Body Weight and Composition:* A trained researcher will collect body weight and measures of body composition (fat-free mass, fat mass, bone mass) using a validated bioelectrical impedance (BEI) scale in OCTRI’s Clinical and Translational Research Center (CTRC).

*Vital Signs:* A trained researcher in the same clinic space will record participant body temperature, pulse rate, respiration rate, and resting blood pressure. Blood pressure will be measured using a calibrated instrument after 5 minutes of quiet sitting using an appropriately sized arm cuff.

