*Safety Labs and Biomarker Samples:* Chemistry and hematology panels, lipids, A1c, blood glucose, and creatinine clearance labs will be obtained via venous blood samples that will be collected to further measure the safety profile of the intervention. Additional blood will be drawn for biomarker analysis to assess intervention efficacy and exploratory effects (Table 2). A total of 60 mL of blood will be drawn. These samples will be collected while fasting by a certified phlebotomist in the OCTRI CTRC outpatient clinic.

*In-Lab Demographics and Health Behaviors Surveys:* At baseline, participants will complete a demographics and health behavior survey and at follow-up they will complete a shorter version of the same health behaviors survey.

*Montreal Cognitive Assessment:* A trained researcher will administer the Montreal Cognitive Assessment (MoCA), a validated test used to measure cognitive function, at the baseline and follow-up visits.

*Unified Huntington’s Disease Rating Scale (UHDRS):* The UHDRS is a clinical rating scale developed to assess four domains of HD – motor function, cognitive function, behavioral abnormalities, and functional capacity. The scale will be used to track and assess for clinical effects of TRE. The assessment consists of four parts with separate scoring for each part:

Part I: Motor function. 31 items with 5-point ordinal scale ranging from 0-4 that indicates performance on motor tasks.

Part II: Cognitive function. Three items including the Verbal Fluency Test, Symbol Digit Modalities Test, and the Stroop Interference Test that evaluate cognitive performance.

Part III: Behavioral assessment. 10 items with a 5-point ordinal scale ranging from 0-4 that indicates the severity of behavioral symptoms associated with HD.

Part IV: Functional capacity. This domain is divided into three sections:

1. Huntington’s Disease Functional Capacity Scale (HDFCS) is reported as the Total Functional Capacity Score (TFC) which has a total of 25 yes/no questions assessing the total functional capacity of the individual.
2. Independence Scale rated from 10-100 indicating functional level of independence.
3. Functional capacity assessment consisting of five items with a 4-point ordinal scale ranging from 0-4.

A trained medical professional will complete the total UHDRS with each participant in the OCTRI CTRC outpatient clinic.

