**Table 2. Biomarker Analysis**

| **Primary Outcome Measures** | | | | |
| --- | --- | --- | --- | --- |
| **Biomarker** | **Definition** | **Measurement** | **Indication for Use** | **Method** |
| Neurofilament light protein (NfL) | A protein component of the neuronal cytoskeleton released into the CSF and blood from damaged neurons | A serum biomarker of neurodegeneration in HD, correlates with disease onset, stage, severity, and progression [26, 27] | Proof-of-concept measure of efficacy | ELISA or Single-molecule array (SIMOA) |
| Glial fibrillary acidic protein (GFAP) | A protein of astrocytes, increased in astroglial activation | A serum biomarker of neurodegeneration in HD, correlates with NfL, disease stage, and progression [28] | Proof-of-concept measure of efficacy | ELISA or Single-molecule array (SIMOA) |
| **Secondary Outcome Measures** | | | | |
| Peripheral mutant huntingtin protein (mHTT) | A protein known to play a critical role in the pathogenesis of HD | A leukocyte biomarker that correlates with HD severity, onset, and progression [29-31] | Exploratory mechanism of action measure | ELISA-based MSD |
| ULK1 | A mammalian serine/threonine protein kinase, plays a key role in the initial stages of autophagy | mRNA expression of ULK1 correlates with autophagic activity, potentially upregulated by TRE [32, 33] | Exploratory mechanism of action measure | qPCR |
| NRF2 | A transcription factor that regulates endogenous antioxidant response pathways | mRNA expression of NRF2 correlates with ROS response, upregulation has therapeutic indications in HD, potentially upregulated by TRE [34-36] | Exploratory mechanism of action measure | qPCR |
| Bioenergetic profile | A description of cellular energy metabolism characteristics | A measure of mitochondrial function and ETC activity, altered in HD, and potentially improved by TRE [37] | Exploratory mechanism of action measure | Seahorse analyzer |

7. Data and Specimens

- 1. Handling of Data and Specimens
     1. **Electronic Data Handling**: While the study is active, all PHI will be stored in a database housed on a secure OHSU server. PHI will be accessible to only investigators, and research staff listed on the protocol. No PHI will be stored or transferred via USB or other portable drives. We will obtain a waiver of the HIPPA authorization requirement for PHI collect at the time of the phone and survey screen.

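### Visit-day fasting is not standardised between baseline and follow-up, so changes in weight, fat-free mass and several blood measures may be confounded with hours since the last intake

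*Protocol*

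**What the plan says.** **Blood.** Protocol Section 6 (Safety Labs and Biomarker Samples): "These samples will be collected while fasting by a certified phlebotomist in the OCTRI CTRC outpatient clinic". No number of hours, no clock time and no matching of the two visits is given there or elsewhere.

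**Weight and impedance.** Section 6 (Body Weight and Composition): "A trained researcher will collect body weight and measures of body composition", with the components listed as "fat-free mass, fat mass, bone mass) using a validated bioelectrical impedance (BEI) scale". No fasting, hydration or time-of-day condition is attached. The next paragraph does set a condition for blood pressure (a seated rest of 5 minutes and a suitable cuff size), so visit conditions are treated as protocol content.

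**Eating pattern before TRE.** Baseline comes before TRE starts, and Section 5 excludes people who "Have consistently practiced a time-restricted eating protocol within 3 months of trial onset".

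**Eating pattern under TRE.** Section 6 (Time-Restricted Eating Protocol): "Outside of that window, for the remaining 16-18 hours of day/night, participants will be asked not to consume calorie-containing food or drink". On the placing of the window: "Participants will be allowed to self-select the timing of the eating window, but once selected, should attempt to maintain the schedule", on at least 5 days in 7.

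**Follow-up.** Section 4 places the visit within 7 days after week 12, with no time of day. Sections 2 and 4 give TRE as 13 weeks (+/- 1 week). The Time-Restricted Eating Protocol paragraph in Section 6 gives 12 weeks.

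**Analysis.** The trial has one arm (Section 4). Section 8 compares baseline with follow-up by paired t-tests, and percent change in weight and fat-free mass is the primary safety outcome.

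**The concern.** In most trials a loose fasting rule adds noise that has nothing to do with treatment. Here the intervention is itself a change in the timing of food, so the hours since the last intake can differ systematically between the two visits. With one arm, nothing subtracts such a shift. Because the condition is set on the visit day, it cannot be restored at analysis, least of all if the time of last intake was never recorded.

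Two groups of results are exposed.

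- **Safety.** Weight and impedance-derived fat-free mass may depend on gut content and hydration, and neither measurement has a stated condition. Section 6 also tells participants on TRE to take ample water and electrolytes, a further possible difference between visits. Fasting glucose and lipids are named in Hypothesis 2.
- **Mechanism.** Table 2 justifies ULK1 on the ground that "mRNA expression of ULK1 correlates with autophagic activity, potentially upregulated by TRE" and gives a similar reason for NRF2 and the bioenergetic profile. A change that followed one longer fast before the draw could not be told from an effect of 12 weeks of TRE.

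No such argument is made here for NfL and GFAP, and A1c, which measures longer-term glucose, need not be affected.

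**Working it through.** **1. The plan's own weight figure.** Inputs from Section 8 (sample size): difference 2.5%, SD 2.4%, n=15, two-sided alpha 0.05.

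- SE = 2.4/√15 = 0.620%
- Noncentrality = 2.5/0.620 = 4.03; critical t on 14 df = 2.145
- Power from the noncentral t = 96.3%, against 95% stated

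The figure reproduces to within 2 points and is not in dispute. The same test is used in step 3.

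**2. How far the fast at the visit could differ.** The protocol gives neither the clock time of the draw nor habitual meal times. Assume an 08:00 draw at both visits and a last intake at 20:00 to 22:00 before baseline, which is a fast of 10 to 12 h.

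| Window before follow-up | Fast at 08:00 | Difference from baseline |
|---|---|---|
| 08:00-14:00 | 18 h | +6 to +8 h |
| 08:00-16:00 | 16 h | +4 to +6 h |
| 12:00-20:00 | 12 h | 0 to +2 h |
| 14:00-22:00 | 10 h | -2 to 0 h |

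All four windows are permitted. Across them the difference runs from 2 h shorter to 8 h longer. A longer fast at follow-up is possible, but neither certain nor uniform.

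**3. What a visit-day shift could do to the weight test.** The protocol gives no size for a fasting effect on weight, so the mean shifts below are assumptions. SD is 2.4% and true change is zero.

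- n=20: SE = 2.4/√20 = 0.537%; critical t on 19 df = 2.093
- n=15: SE = 0.620%; critical t on 14 df = 2.145
- Noncentrality = shift/SE

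| Assumed mean shift | Share of the 2.5% design difference | Noncentrality, n=20 | Significant, n=20 | Significant, n=15 |
|---|---|---|---|---|
| 0 | 0 | 0 | 5% | 5% |
| 0.25% | 10% | 0.47 | 7% | 7% |
| 0.5% | 20% | 0.93 | 14% | 12% |
| 1.0% | 40% | 1.86 | 42% | 32% |

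The shift is the mean over all participants. If only half were affected, by 1.0% each, the mean would be 0.5% and the n=20 figure about 14%, holding the SD at 2.4%.

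**4. Whether TRE is still running at follow-up.** If TRE lasts 12 weeks, a visit up to 7 days later may find some participants back on their former meal times, and the difference in step 2 could vanish. If it lasts 13 weeks (+/- 1 week), most would still be on TRE. The statements conflict, so the condition at follow-up is not fixed on this point either.

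**The case against.** A reader might infer something stronger: that participants come to follow-up after a 16-18 h fast, so the follow-up values do reflect a longer fast, always in the same direction. The protocol does not support this. The 16-18 h is the full daily fast, not the time since food at the appointment. Step 2 shows that a late window can give no excess, or a shorter fast than at baseline. Nor does the fasting rule cover the whole visit: it applies to blood only, and weight and impedance have no rule at all.

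Other points on the sponsor's side:

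- **The shifts in step 3 are assumed.** This stands. The 42% is not an expected error rate.
- **The safety thresholds hardly move.** Section 2 allows up to 10% loss of weight and 5% of fat-free mass, and Section 11 mentions a small weight loss, not expected to exceed 2.5%. Applying the weight SD of 2.4% to fat-free mass (an assumption) with a normal distribution, the chance that one participant exceeds a 5% loss is Φ(-5/2.4) = 1.9% with no shift and Φ(-4/2.4) = 4.8% with a 1.0% shift. In that direction the error is also towards a false safety alarm. This largely stands for the threshold hypothesis, but Section 8 makes the paired t-test the primary safety analysis.
- **Home weights give a second series.** True for weight, but they are self-reported, have no stated condition, and say nothing about fat-free mass or blood.
- **Non-caloric drinks are allowed, so TRE does not restrict fluid.** This stands, but it does not match hydration at the two visits.
- **The daily survey records when eating stops.** It begins in the lead-in, after the baseline visit, so the baseline fast is not captured.
- **ULK1, NRF2 and bioenergetics are exploratory.** This lowers the stakes for those measures but does not remove the confounding.

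**Conclusion.** The point holds as possible confounding. The protocol fixes neither the length of the fast nor the clock time for the blood draws, sets no condition for weight and impedance, and does not match the two visits. The intervention changes meal timing and there is no control arm, so a change in the affected measures cannot be cleanly assigned to 12 weeks of TRE.

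The direction is not established and the documents give no size. The 7, 14 and 42% for assumed mean shifts of 0.25, 0.5 and 1.0% show only how sensitive the test is at n=20. They rest on the protocol's SD of 2.4%, no true change, and shifts chosen for illustration. No sample-size figure changes. This is a cheap improvement that should be made before data are collected.

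**What to change.** In Section 6:

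1. For each participant, use the same morning clock-time slot and the same hours since last calories (within about 1 h) at both visits. Moving the appointment alone cannot match both when the window is early: after an intake ending at 16:00, a 10-12 h fast would put the draw at 02:00 to 04:00. Instead, time the last intake on the evening before follow-up to match the recorded baseline fast. The existing allowance to keep the chosen schedule on at least 5 of 7 days leaves room for this.
2. Measure weight and impedance in that same fasted state, before the blood draw.
3. Record the time of last calories and of last fluid at both visits, since the daily survey does not reach back to baseline.
4. Reconcile the 12-week and 13-week (+/- 1 week) statements in Sections 2, 4 and 6, so that it is clear whether TRE is still running at follow-up.

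The cost is a scheduling instruction and two recorded times per visit. Appointments become slightly less flexible, and some participants will shift one eating window before the visit. No extra procedure or staff is needed.
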